### Training and supervision of LPs

 LPs will be bachelor’s degree students in psychology or a related field and will have no post-graduate training in a specialized mental health program. They will be recruited through interviews to assess communication and interpersonal skills. Training will be divided into 2 successive steps spread over a period of one to 2 weeks. The first step (6 hr) will consist of readings on GAD in older adults, basic helping relationships skills, and the GSH-CBT participants’ manual. The second step (4.5 hr) will consist of didactic training, including demonstrations, role plays, and feedback,  on the support to be provided by LPs to participants. LPs will be informed of the procedures used for ongoing biweekly supervision of their work by a licensed psychologist, namely authors PL, PG, and SG, depending on study site. They will also be informed of the crisis protocol to be applied in the event of a worsening of the participant’s condition (e.g., suicidal risk, severe depressive symptoms). This protocol will involve reporting the situation immediately to the psychologist, who will follow up with the participant. In addition, a meeting with all LPs involved in the study will be held once a year to discuss practical issues and hence maximize cohesion between the three sites. Similar meetings will be held with research assistants conducting assessments to ensure that they follow the evaluation process and to answer their questions.

### Procedure

After initial telephone screening and clinical psychological assessment, eligible individuals will sign the consent form and answer self-administered questionnaires. The schedule of enrolment, interventions, and assessments is shown in Table 2. Participants will complete self-administered questionnaires at home and will have the choice between paper or online questionnaires. Persons who are found not eligible for the study but who would like help with a personal difficulty will be referred to an alternative resource.

**Table 2 Tab2:**
[figure not shown]
Schedule of Enrolment, Interventions, and Assessments

*ADIS-5* Anxiety and Related Disorders Interview Schedule for DSM-5, *A-Lit* Anxiety Literacy Questionnaire, *CAQ* Cognitive Avoidance Questionnaire, *CEQ* Credibility/Expectancy Questionnaire, *GAI* Geriatric Anxiety Inventory, *GDS* Geriatric Depression Scale, *ISI* Insomnia Severity Index, *IUI* Intolerance to Uncertainty Inventory, *NPOQ* Negative Problem Orientation Questionnaire, *PSWQ* Penn State Worry Questionnaire, *QBMA* Questionnaire of Behavioral Manifestations of Anxiety, *SDS* Sheehan Disability Scale, *SSQ6* Short version of Sarason’s Social Support Questionnaire, *T-MMSE* Telephone version of Mini-Mental State Examination, *TMQ* Treatment Motivation Questionnaire, *W* week during treatment or waiting period, *WAI* Working Alliance Inventory, *WAQ* Worry and Anxiety Questionnaire, *WWQ* Why Worry Questionnaire

A block randomization procedure stratified on diagnosis will be used. The randomization sequence will be determined prior to recruitment by the project coordinator. Block size will be fixed at 4, all possible balanced combinations of assignments within a block will be identified, and blocks will be randomly chosen to determine participants’ assignment to groups. Randomly assigned conditions will be sealed in envelopes labelled with participant codes and opened by the project coordinator following completion of the pre-treatment assessment. Group assignment will be done separately for participants with threshold and subthreshold GAD. Participants assigned to the experimental group will begin treatment immediately after the pre-treatment assessment. Participants assigned to the control group will have a 15-week wait period, during which they will receive a 15-min telephone call from the local professional research assistant on four occasions separated by four-week intervals. The purpose of these calls is to encourage the participant to persevere until the start of treatment and to identify potential negative effects that could be associated with the waiting period. For the experimental group participants, assessments will take place at pre- and post-treatment and at 6 and 12 months post-treatment. For control group participants, three assessments are planned: two at pre-treatment (before and after the waiting period) and one after receiving treatment (post-treatment). All participants will receive financial compensation ($20 CAD) for each of the post-treatment and follow-up assessments to support participation in post-treatment assessments.

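### The project coordinator both generates the allocation sequence and opens the envelopes, and a fixed, published block size of 4 lets anyone who tracks a whole diagnosis stratum be certain of up to one third of assignments

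*Protocol article*

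**What the plan says.** The allocation procedure is set out in the protocol article under Methods, Procedure.

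- **Who makes the list, and its block size:** "The randomization sequence will be determined prior to recruitment by the project coordinator. Block size will be fixed at 4". Each block is drawn from all the balanced orderings.
- **Who reveals the assignment:** conditions are "sealed in envelopes labelled with participant codes and opened by the project coordinator following completion of the pre-treatment assessment". The article does not say who keeps the envelopes until then.
- **Stratification:** "A block randomization procedure stratified on diagnosis will be used", and "Group assignment will be done separately for participants with threshold and subthreshold GAD". Site is not named as a stratum, although Trial design gives three sites that each recruit into both groups.

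Other sections show who decides on entry and who sees the assignments.

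- **Screening:** the site's professional research assistant (Initial telephone screening).
- **Diagnosis, which fixes the stratum:** independent research assistants, supervised by independent clinicians, with every interview recorded (Telephone clinical psychological assessment).
- **Mailing treatment material:** the site's professional research assistant (Treatment).
- **Calls during the wait:** the local professional research assistant makes four calls to each control participant (Procedure).

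**The concern.** Allocation is concealed when nobody who can affect whether, when or in which stratum a person enters knows the next assignment. Two features of the procedure weaken this.

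First, a sealed envelope hides nothing from the person who wrote the list. Opening it after baseline protects against staff who do not know its content, but not against the coordinator. The article names no independent person for either generating the sequence or revealing the assignment.

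Second, a fixed block of 4 can be decoded by anyone who follows the history. In a wait-list trial each assignment becomes visible once it is made. The site assistant who screens also mails the treatment material and telephones the waiting participants, and so learns past assignments.

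Some entry decisions involve judgement. Under Participants, a comorbid case is admitted or not according to how far its interference rules out starting with generalized anxiety, and subthreshold GAD is defined by how many of three features are present. Foreknowledge could affect who is encouraged to enter, and when. What is at stake is selection bias, and with it the comparability of the groups at baseline.

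**Working it through.** The article gives no predictability figure, so there is none to reproduce.

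**Inputs.** Allocation is 1:1 (45 per group, Participants). The block size is 4 and there are two diagnosis strata (Procedure). There are three sites (Trial design), and 130 people are to be admitted (Participants).

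**1. Observer who knows the block boundaries and every earlier assignment in the stratum.** A position is certain once one arm has filled its two places. With E for experimental and W for wait-list, the six balanced orderings give:

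| Ordering | Certain positions |
|---|---|
| EEWW | 2 |
| WWEE | 2 |
| EWEW | 1 |
| EWWE | 1 |
| WEEW | 1 |
| WEWE | 1 |
| Total | 8 of 24 = 33.3% |

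For 130 admitted, 130 × 1/3 ≈ 43 assignments.

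**2. Best guess.** Guessing the arm that is behind, with a coin toss when the arms are level, is right with these probabilities:
- position 1: 1/2
- position 2: 2/3
- position 3: (2/3)(1/2) + (1/3)(1) = 2/3
- position 4: 1

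The sum is 2.833, and 2.833/4 = 70.8%, against 50% by chance.

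**3. Observer who sees only one site's assignments.** Assume one list per stratum shared across sites, and let p be each site's share of entries. Generously, let the observer also know the block boundaries. A position that would be certain to a full observer stays certain only if the two assignments that fill the arm were made at the observer's own site. The certain share is therefore (1/3) × Σp³.
- Equal sites: (1/3) × 3 × (1/3)³ = 1/27 = 3.7%, or about 5 of 130.
- Shares 50/25/25: (1/3) × (0.125 + 0.0156 + 0.0156) = 5.2%, or about 7 of 130.

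A simulation of 200,000 blocks gives the same values (3.7% and 5.2%). If the lists were run separately by site, the share returns to one third at each site.

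**4. The coordinator.** The person who made the list can know up to 100% of it in advance.

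**5. Effect of varying the block size.** This is a simulation of lists of 65 participants, with an observer who knows which sizes are in use and updates on the full history. The fixed-4 row is the exact result from steps 1 and 2.

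| Block sizes | Certain | Best guess right |
|---|---|---|
| Fixed 4 | 33.3% | 70.8% |
| 4 and 6 at random | 5.5% | 68.9% |
| 4, 6 and 8 at random | about 2% | about 68% |

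Varying the size removes most of the certainty but little of the advantage from guessing.

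**The case against.** The strongest case on the other side is that the article already separates the decisions that matter. It gives the coordinator no role in screening, diagnosis or stratum. Screening belongs to site assistants. The diagnosis is made by independent, supervised and recorded assessors, trained alike and with the same supervisors at all sites. The sequence is fixed before recruitment, the envelopes are sealed, and they are opened only after screening, assessment, consent and baseline questionnaires. All of this stands and limits the risk. For staff other than the coordinator, late opening of a sealed envelope is a real safeguard.

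Four stronger readings might be inferred, and the documents do not support them.

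- **The coordinator holds the envelopes.** The article says only who opens them.
- **One third of assignments are predictable to anyone.** That figure requires the whole stratum history and the block boundaries. It is too high for a single-site observer of a shared list and too low for the list's author.
- **Borderline cases can be steered into a convenient stratum.** This would require the coordinator to disclose the list to, or override, recorded and supervised assessors. Nothing in the article describes that.
- **Better concealment would deal with self-reported outcomes in a wait-list comparison.** Expectancy and reporting bias are a separate problem, which concealment does not cure.

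It is also fair to say that envelope opacity, numbering and release logs are details that an article commonly leaves to the full protocol. Their absence is not part of this point, which rests on what the article states.

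The objection leaves two things unanswered. The author of the list cannot be blind to it, and no barrier to contact with screening staff is described. The people who screen also learn earlier assignments.

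**Conclusion.** The point holds as a weakness in the stated procedure, not as evidence that bias has occurred. Sequence generation and envelope opening rest with one trial-team member, from whom allocation is therefore not concealed. The fixed, published block size makes up to 33.3% of assignments certain to someone with the full history of a stratum. For a single-site observer the share is about 4 to 5% if lists are shared across sites, and one third if they are run by site. The article does not say which applies; stratification on diagnosis alone suggests shared lists, but that remains an assumption. The 4 to 5% range also assumes the site shares shown and known block boundaries.

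The route to bias would be disclosure or influence by the coordinator, or inference by screening staff from past assignments. The article neither describes nor rules out either one. The change is worth making because it is cheap, and most of its benefit comes from separating the roles.

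**What to change.** For all remaining assignments:

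1. Have an existing person with no role in recruitment, screening, assessment or enrolment (for example, a university statistician or data manager) generate and keep the sequence.
2. Vary the block size at random, for example 4 and 6, within each diagnosis stratum, and do not disclose the sizes to the study team.
3. Release each assignment singly, only after the stratum and the completed baseline have been logged.
4. State whether the lists are shared across sites or run by site, and who had access to the list and the envelopes.
5. In the results paper, report how many participants were randomised under each procedure.

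The cost is a few hours of existing staff time and a procedural amendment, with no added assessments. The imbalance at the end of a list could be slightly larger, and participants already randomised keep the old scheme. The benefit depends on how many assignments remain, which the article does not say; its Discussion shows that participants were already in treatment in spring 2020. If recruitment has ended, only the reporting in item 4 can still be done.

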**Methods:**

We will conduct a multisite randomized controlled trial comparing an experimental group receiving GSH-CBT guided by LPs (*n* = 45) to a wait-list control group (*n* = 45). Treatment will last 15 weeks and will be based on a participant’s manual. Weekly telephone sessions with LPs (30 min maximum) will be limited to providing support. Data will be obtained through clinician evaluations and self-assessment questionnaires. Primary outcomes will be the tendency to worry and severity of GAD symptoms. Secondary outcomes will be anxiety symptoms, sleep difficulties, functional deficit, diagnosis of GAD, and cognitive difficulties. For the experimental group, measurements will take place at pre- and post-treatment and at 6 and 12 months post-treatment. For the control group, three evaluations are planned: two pre-treatment evaluations (before and after the waiting period) and after receiving treatment (post-treatment). The efficacy of GSH-CBT will be established by comparing the change in the two groups on the primary outcomes.

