### Treatment

Treatment will be the same as used in our previous study [33]. All treatment material will be sent to participants by the site’s professional research assistant. Prior to beginning treatment, the LP will contact the participant, ensure that he has received the material, briefly explain how the treatment works, tell the participant that he can start and make an appointment with him for the first telephone session. Complete treatment duration will be 15 weeks and be based on a participant’s manual consisting of eight modules. The main components of treatment are relaxation, differentiation of the main types of worries, learning to tolerate uncertainty, questioning false beliefs about worries, problem solving, cognitive exposure, and planning pleasant activities. The content of the modules is presented in Table 1. Each module will be the topic of one to three telephone sessions with the LP, at the rate of one session per week. The participant will be asked to read the corresponding module each week and do the recommended exercises. The sessions with the LP will be limited in duration (30 min maximum) and the role of the LP will be restricted to providing support within treatment procedures, namely motivational support (motivate the participant to continue treatment), emotional support (make the participant feel he is understood), and technical support (track activities done and to be done and answer technical questions related to treatment). Each session will follow an identical sequence: it will begin with a summary of the activities completed since the last session, followed by answering participant’s questions and finishing with planning the next week’s activities. LPs will not be allowed to practice psychotherapy in any form including applying techniques to modify participant’s beliefs and behaviors such as described in the treatment manual.

**Table 1 Tab1:** Content of the Modules

Module Title	Number of sessions	Content
1. Therapy goals and basic components of anxiety	1	• Therapy characteristics • Key elements for success • The two types of worries
2. Relaxation	1	• Abdominal breathing • Progressive muscle relaxation • Imagery
3. Tolerating uncertainty	3	• Exposure to uncertainty
4. Enjoying yourself	2	• The relation between anxiety and depression • Identification of pleasant activities • Planning pleasant activities
5. Correcting false beliefs	1	• Questioning false beliefs about worrying

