### Data management and analysis

The principal investigators (PL, PG, and SG) will have access to all trial data. To protect the identity of participants and confidentiality of information, participants will be identified by a code number. Data obtained by paper questionnaires will be kept in a secure file. Data in electronic format will be kept on a secure server accessible to the research team only. Research assistants will double-entry data in paper format in order to detect and correct data entry errors. Data obtained from online questionnaires will be added to the data files.

SPSS for Windows will be used for statistical analyses. Missing data will be handled using multiple imputation. Descriptive analyses of study variables will be carried out. Analyses will follow intention-to-treat principles (i.e., data from all participants included in the study will be analyzed according to the randomization scheme). The pre- and post-treatment data will be used to compare the experimental and control groups. Repeated measures analysis of variance (ANOVA) will be performed on most outcome measures. Simple effects for group and time and group by time interactions will be analysed. Between group comparisons will include remission rate based on GAD diagnosis using the chi square test and clinically significant change which will be examined according to procedures described by Jacobson et al. [65, 66]. Change on the Sheehan Disability Scale will be analysed according to Sheehan and Sheehan’s [67] criteria. In order to determine whether the effects of the treatment are sustained over time, the post-treatment, 6 and 12-month data of the experimental group will be used. Repeated measures ANOVA will be carried out on the different variables and followed by contrast analyses. All model assumptions will be checked. Participants’ and LPs’ perception of treatment will be analyzed by calculating the frequency of each answer choice for the various statements and by summarizing comments.

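### As worded, the $20 payment covers the 15-week assessment in the experimental arm but not the matching end-of-wait assessment in the control arm

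*Protocol article*

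**What the plan says.** All of the payment text is in the protocol article, Methods, Procedure, in the paragraph on randomisation and assessments after Table 2. The rule is that "All participants will receive financial compensation ($20 CAD) for each of the post-treatment and follow-up assessments", and its stated aim is "to support participation in post-treatment assessments".

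The same paragraph sets the assessment labels. For the experimental group, "assessments will take place at pre- and post-treatment and at 6 and 12 months post-treatment". For controls there are three assessments: "two at pre-treatment (before and after the waiting period) and one after receiving treatment (post-treatment"). The Abstract (Methods) labels them the same way: "two pre-treatment evaluations (before and after the waiting period) and after receiving treatment (post-treatment"). Controls have no 6- or 12-month follow-up.

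The two periods being compared are of equal length. In Treatment, "Complete treatment duration will be 15 weeks"; in Procedure, "Participants assigned to the control group will have a 15-week wait period". Data management and analysis then states that "The pre- and post-treatment data will be used to compare the experimental and control groups".

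**The concern.** The efficacy comparison needs outcome data from both arms at about 15 weeks. For controls, that means the end-of-wait assessment, since their later one follows their own treatment. The self-report questionnaires, which include both primary outcomes, are completed at home on paper or online, so whether a participant bothers to return them matters.

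The protocol itself treats payment as a means of supporting response. If the rule is applied as worded, that support goes to one arm only at the time point that decides efficacy. Response may then differ between arms in how many answer, in who answers, or in both. With 30% drop-out expected, there is room for this to matter.

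Multiple imputation is planned. A difference in response rate does no harm in itself if arm is in the imputation model. Harm arises when non-responders differ from responders in outcome in ways that the observed data do not explain.

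**Working it through.** The point rests on wording, and the plan gives no figure for it. The first step sets the sentences side by side; the later steps only gauge size.

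**1. Which assessments are paid, on the article's own labels**

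| Assessment | Experimental | Control |
|---|---|---|
| Before randomisation | pre-treatment, unpaid | first pre-treatment, unpaid |
| About 15 weeks | post-treatment, $20 | second pre-treatment (end of wait), unpaid |
| After delayed treatment | not applicable | post-treatment, $20 |
| 6 and 12 months | follow-up, 2 x $20 | none |

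Totals are 3 x $20 = $60 and 1 x $20 = $20. Most of that gap reflects the different number of assessments and is not the issue. The issue is the second row, $20 against $0. Nothing in the visible text says that the end-of-wait assessment is paid.

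**2. The term post-treatment in the analysis section.** Data management and analysis compares the groups on pre- and post-treatment data. For controls, post-treatment can there only mean the end-of-wait assessment. The article therefore uses the term in two senses, and the payment sentence does not say which applies.

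**3. People at risk of being missing.** The Participants section admits 130 to retain 90 at 30% drop-out: 90 / (1 - 0.30) = 128.6, so the stated 130 is consistent. With balanced blocks that is 65 per arm. Expected drop-outs are 130 x 0.30 = 39, about 20 per arm.

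**4. Possible bias (assumed inputs).** If the gap between responders and non-responders that imputation does not capture is the same in both arms,

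bias = (difference in missing proportion) x (uncaptured gap in SD).

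The documents give neither input. I assume a response shift of 5 to 15 percentage points in one arm (0.05 x 65 = 3.25 to 0.15 x 65 = 9.75, about 3 to 10 people) and a gap of 0.3 to 0.5 SD.

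- Low: 0.05 x 0.3 = 0.015 SD, and 0.015 / 0.65 = 2.3% of the planned effect.
- High: 0.15 x 0.5 = 0.075 SD, and 0.075 / 0.65 = 11.5% of the planned effect.

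The sign depends on which arm loses more responders and whether those lost are better or worse off. Neither is known.

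**5. Power (two-sided t-test, alpha 0.05, effect 0.65, 65 per arm; drop-out by arm assumed)**

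| Drop-out, experimental / control | Power |
|---|---|
| 30% / 30% | 0.87 |
| 30% / 40% | 0.84 |
| 30% / 50% | 0.80 |

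The first row exceeds 0.80 because 45 per group is more than the 39 that this test needs. Power is not the concern.

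**The case against.** A reader might infer that the trial in fact pays only the experimental arm at 15 weeks. The article does not establish that. The payment sentence opens with all participants, the analysis section extends post-treatment to the controls' end-of-wait data, Table 2 is not shown, and payment terms per visit normally sit in the full protocol and consent form, which are also not shown. This objection stands: the defect is in the wording, and actual practice is unknown. It does not remove the need for a correction. The words about all participants say who is paid, while the labels in the preceding sentence say for what.

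It can also be argued that the imbalance may run the other way. Controls have treatment ahead of them and receive four calls meant to keep them in until it starts, whereas experimental participants have finished treatment by week 15. A payment in that arm alone could narrow a response gap. This stands against any claim about direction. It does not make the inducements equal, and the article nowhere presents the difference as deliberate.

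A further inference would be that the controls' existing $20 is wasted on an assessment outside the randomised comparison, and could be moved to the end of the wait. The documents contradict this. The predictor analysis combines both groups' pre- and post-treatment data, and Trial design gives this use of the controls' data as a benefit of the wait-list arrangement. Moving the payment would weaken a stated secondary goal.

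Finally, the plan has safeguards: intention-to-treat analysis, multiple imputation, and a request that withdrawing participants complete the instruments once more. These reduce the risk but do not equalise the inducement.

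**Conclusion.** The point holds as a flaw in wording with a possible design consequence. On a literal reading, the stated rule pays one arm only at the assessment pair that forms the randomised comparison, and no visible text corrects it. Whether sites applied it that way cannot be told from the article.

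The documents do not support saying that the comparison is biased. There is a risk of arm-dependent response whose direction is unknown. The range of 0.015 to 0.075 SD rests wholly on assumed response shifts and gaps, and on imputation failing to capture those gaps. It is small beside 0.65 SD. The case for acting is that the arm difference is avoidable and cheap to remove.

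**What to change.** Reword the payment sentence in Procedure to name the assessments by arm. The $20 is paid for the 15-week assessment in both groups, meaning post-treatment for the experimental group and end of waiting period for the control group. Keep the payments for the controls' assessment after their own treatment and for the experimental group's 6- and 12-month follow-ups.

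The cost is at most 65 x $20 = $1,300 CAD, plus an ethics and consent amendment. The article indicates that the trial was already under way, since items on COVID-19 were added during the study. A change would then reach only controls not yet assessed at the end of their wait, and 15-week response should also be reported by arm. If controls have been paid at that point all along, only the wording needs correcting and no payment cost arises.
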